#### 2.5.3. Additional Outcomes

Where available, results of the detailed follow-up sub-study of STEPCARE at 6 months and 12 months will also be used in the analysis of V-CARE; they include measures of cognition (MoCA, SDMT, MFIS IQCODE-CA—patients only), burden (ZBI—key supporters), anxiety and depressive symptoms (HADS—both), post-traumatic stress symptoms (PCL-5—both), health-related quality of life (EQ-5D-5L, WHODAS 2.0—both), life satisfaction (both), and detailed questions about return to work/rehabilitation (patient only) [43].

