### 2.6. Data Collection, Statistical Analyses, and Sample Size

For primary outcomes, descriptive statistics will be used to report on recruitment and retention rates. Continuous variables will be presented as the mean (SD) or median (IQR) depending on the distribution of data and percentages for categorical variables.

Using the methodology described by Lewis et al. [44], we set up hypothesis testing around progression criteria that tests against being in the ‘red zone’ based on an alternative of being in the ‘green zone’. Specifically, we aim to investigate that a true feasibility/tolerability outcome is not greater than the upper ‘red limit’ (null hypothesis) vs. a true feasibility/tolerability outcome that is greater than that (alternative hypothesis). Criteria for success and a traffic light system to identify the need for amendment for a fully powered trial are as follows:Feasibility: At least 35% of patients screened as eligible should be recruited into the trial (green), but the trial will not be feasible if recruitment uptake is 20% or less (red). Recruitment of between 20% and 35% may require amendments (amber).Tolerability: The drop-out rate of patients recruited in the trial should be 20% or less (successful completion of the trial is defined as taking part in at least 3 out of 4 sessions of the intervention and complete outcome measures). A drop-out rate of 40% or more will indicate that the full trial is not feasible (red), with a percentage between 20% and 40% suggesting that amendments may be required (amber).Satisfaction with care: No more than 30% of participants in the V-CARE arm should score less than 24/32 on the CSQ-8 (green); if more than 60% of participants score less than 24/32, this will indicate that the trial is not feasible (red), with a percentage between 30% and 60% suggesting that amendments to the protocol may be required (amber) (Figure 1).

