A sample size calculation using a one-tailed test with alpha = 0.05 and beta = 0.9 identifies that with reference to the three criteria highlighted in this section, respectively, 78, 131, and 143 participants would be needed to be screened in order to meet the individual power requirement of > 90% (with regard to the second and third criterion, this is based on the assumption of only 35% of screened patients being actually randomized (2), and only half of these patients being in the intervention arm (3)). For this reason, we aim to screen at least 145 participants and recruit at least 50 (25 in each arm). This sample size is considered adequate to estimate key parameters to inform the design of an RCT.

To assess differences between two groups, the analyses will be conducted using independent data, with tests appropriate to the distribution of the data (independent *t*-test or Mann–Whitney U test). Estimated effect sizes (with 95% confidence intervals) for difference will be calculated. All *p*-values will be unadjusted for multiple comparisons due to the exploratory design [45]. Multi-variable logistic regression models will be used to evaluate the associations between disease severity, sociodemographic variables, and outcome measures. Outcomes will be statistically controlled for potentially confounding variables such as age, sex, education, and length of intensive care stay. As this is a feasibility study, the study will be underpowered; therefore, no conclusions on the effectiveness of the intervention will be made. SPSS v 29.0 or above will be used to analyze the data.

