## 3. Conclusions

In this manuscript, we present the protocol for a multi-centre, randomized pilot trial investigating if a remotely delivered psychoeducational intervention for OHCA survivors and their key supporters is feasible, and in addition if there is trend towards beneficial effects compared to a control group receiving a digital information booklet only. We describe the different phases of the study, namely the rationale for this intervention, conceptualization of the project, structure of the intervention, and outcome measure adopted. The primary outcome is the evaluation of the feasibility and tolerability of delivering this intervention—definitions have been provided to measure this outcome. Secondary outcome measures include the Client Satisfaction Questionnaire and the Self-Management Assessment Scale. Criteria for the success of the study have been reported, and a description of the pre-planned statistical analyses provided.

The preliminary results from this pilot trial will provide valuable insights to inform a larger trial to evaluate the effectiveness of an intervention to support recovery post-cardiac arrest. First, the outcome feasibility will provide insights regarding the actual interest of patients and their caregivers to take part in a digital intervention to support recovery in the early phase after a cardiac arrest. Second, the outcomes of tolerability and satisfaction with care will be instrumental for the potential need of adjustments in the design of the intervention for the larger trial. Lastly, hypothesis-generating trends in differences between the two groups in terms of self-management skills and health outcomes will be able to guide the choices of primary outcomes and power calculations for a larger trial.

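### For scores taken at both 6 and 12 months, the named two-sample tests cannot use a person's observed visit when the other is missing; a joint two-visit model would do so at little cost (minor)

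*Protocol article*

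**What the plan says.** Protocol article, section 2.5.3 (Additional Outcomes): "Where available, results of the detailed follow-up sub-study of STEPCARE at 6 months and 12 months will also be used". The measures cover cognition, anxiety and depression, post-traumatic stress, quality of life, life satisfaction and supporter burden. Some are taken from patients, some from key supporters and some from both.

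Section 2.6 gives the between-group method: "To assess differences between two groups, the analyses will be conducted using independent data, with tests appropriate to the distribution of the data". The tests named are the independent t-test and the Mann-Whitney U test, with effect sizes and 95% confidence intervals. The section adds: "Outcomes will be statistically controlled for potentially confounding variables such as age, sex, education, and length of intensive care stay". That list is open-ended, but no earlier value of the same score is on it. The only regression named is logistic, and no model links the two visits.

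Section 2.6 also calls the comparisons exploratory and underpowered, and rules out conclusions on effectiveness. Section 3 (Conclusions) nevertheless gives them a use: "hypothesis-generating trends in differences between the two groups in terms of self-management skills and health outcomes" are to guide the primary outcome and power calculation of a larger trial.

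**The concern.** A two-sample test takes one value per person. For a score measured twice, the named method therefore leads most naturally to one comparison at 6 months and another at 12 months, each on those who have that value. Someone seen at 6 months but not at 12 adds nothing to the 12-month comparison, although the 6-month score says something about the missing one.

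There are two consequences. The 12-month estimate is less precise than the data allow. It can also be biased if the people lost differ by arm in their earlier scores. Differential loss is conceivable because one arm has four live group sessions (section 2.4.1) and the other a booklet without a group (section 2.4.2), but the documents do not say that it is expected.

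At stake are the exploratory differences that section 3 carries into the design of the next trial.

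**Working it through.** **The plan's own figures.** The article gives no figure for the 6- and 12-month comparisons. Its only calculation is the number to be screened: 78, 131 and 143 for the three progression criteria. I used a one-sided alpha of 0.05 and read the printed beta of 0.9 as power, since the same sentence requires more than 90% power. An exact one-sample binomial test then gives 77, 45/0.35 = 128.6 and 25/0.175 = 142.9, close to the stated numbers. They rest on the progression criteria alone, so this point does not change them.

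**Inputs.** From the article: two visits, data where available, and a target of 25 per arm. Assumed, because the article gives neither: the 6-to-12-month correlation r, and the fraction m missing at 12 months among people seen at 6 months (the same in both arms). With covariates in the model, r is the correlation that remains after adjustment.

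**Precision.** For a standardised score with complete 6-month data, the variance of an arm's 12-month mean, times the number of people, is:

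- available cases: 1/(1 − m)
- joint model: (1 − r²)/(1 − m) + r²
- ratio, joint to available-case: 1 − r²m

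Example, m = 0.25 and r = 0.7: 1/0.75 = 1.333 against 0.51/0.75 + 0.49 = 1.170. The ratio is 0.8775, a 12% cut in variance.

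| m | r | 1 − r²m | variance cut | standard error cut |
|---|---|---|---|---|
| 0.25 | 0.6 | 0.910 | 9% | 5% |
| 0.25 | 0.7 | 0.878 | 12% | 6% |
| 0.25 | 0.8 | 0.840 | 16% | 8% |
| 0.35 | 0.6 | 0.874 | 13% | 7% |
| 0.35 | 0.7 | 0.829 | 17% | 9% |
| 0.35 | 0.8 | 0.776 | 22% | 12% |

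With m = 0 the ratio is 1: when both visits are complete, the two-visit model without covariates returns the same 12-month contrast as the t-test. A person with neither visit adds nothing to either analysis.

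**Bias.** I simulated 20,000 trials with 25 per arm, r = 0.7 and no true effect. The log-odds of missing month 12 were −1.3 + 1.0 × (6-month score) in one arm and −1.3 in the other. That loses about 25% in the first arm and 1/(1 + e^1.3) = 21% in the second.

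- Dependence in one arm only: the available-case difference is off by about 0.15 SD, the joint estimate by less than 0.01 SD. The empirical standard deviations were 0.320 and 0.306, a cut of 1 − 0.306/0.320 = 4.4%. Repeat runs gave 4% to 5%.
- Opposite dependence in the two arms: about 0.30 SD against less than 0.01 SD.
- The same dependence in both arms: no bias with either method.

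With a weaker dependence (log-odds 0.7 per SD, 27% to 29% missing, r from 0.5 to 0.8), the available-case bias is 0.09 to 0.15 SD for one arm only, 0.18 to 0.29 SD for opposite directions, and zero when the arms match.

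**Scale.** The 95% confidence interval half-width at 25 per arm is 1.96 × √(2/25) = 0.55 SD. A bias of 0.15 SD is about a quarter of that (0.15/0.55 = 0.27).

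**The case against.** The strongest case against is that this is an inference about additional outcomes in a condensed article, with a size that rests on assumed inputs. Much of that stands.

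- A reader might infer that the article prescribes a separate test at each visit. It does not say so. The phrase about independent data most naturally means independent groups as opposed to paired ones, and the sentence is not tied to the 6- and 12-month scores.
- A reader might say that unadjusted tests are the whole plan. They are not, since covariate control is also promised.
- A reader might infer that within-person information is always thrown away. With both visits complete, the 12-month contrast is the same either way. Missing data may also reflect who joined the STEPCARE follow-up sub-study, and people with neither visit gain nothing.
- A reader might infer bias whenever attendance relates to the earlier score. The relation must differ between arms. With no true effect, an equal relation gives none.
- The lack of a named missing-data method is not a finding in itself, because an article commonly leaves that to the full protocol or analysis plan.
- The 6-to-12-month correlation could be calculated from the same data without a mixed model.

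What remains is narrower. The article does name a method for group differences, and section 3 describes the analyses as pre-planned. That method cannot draw on one visit when the other is missing, and an alternative needing no new data exists. The exploratory label limits the consequence but does not remove it, because the estimates are meant to inform the next trial.

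**Conclusion.** The point holds as a minor improvement. As described, the group comparisons make no use of a person's observed score at one visit when the other is missing.

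For correlations of 0.6 to 0.8 and 25% to 35% missing at 12 months, a joint model cuts the large-sample standard error of the 12-month difference by about 5% to 12%. In the simulation at 25 per arm, with less loss and r = 0.7, the cut was 4% to 5%. Available-case bias runs from zero, when loss does not depend on the 6-month score or depends on it equally in both arms, to about 0.15 SD for dependence in one arm and about 0.30 SD for opposite dependence. The joint model removes this bias only if, within arm, loss depends on what was observed and not on the unseen score itself.

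Correlation, missing fraction and pattern of loss are all assumptions. The primary outcomes, progression criteria and sample size are unaffected, and nothing here shows that the 12-month comparisons will in fact be biased.

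**What to change.** For each continuous score taken at both 6 and 12 months, make the main between-arm estimate a linear mixed model: arm, visit, arm-by-visit and the planned covariates as fixed effects, an unstructured 2×2 within-person covariance, REML, and everyone with at least one visit. Fit patients and key supporters separately. Report the arm difference with its 95% confidence interval at each visit, the 6-to-12-month correlation, and the numbers with data by arm and visit.

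Keep the t-test or Mann-Whitney test as a sensitivity analysis for skewed or bounded scores, and as the analysis for the CSQ-8 and SMASc, which have one planned post-intervention comparison.

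Add a sentence on timing. Section 2.4.1 allows delivery up to 6 months after discharge, so some 6-month scores may precede or overlap the intervention, and the 6-month contrast should be read accordingly.

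The cost is a few lines of analysis text. No new data are needed and the planned software fits the model. The downsides are slightly more modelling and a normality assumption for bounded scores in small groups, which the retained tests help to check.

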### 2.3. Study Population and Randomization

In addition to the criteria needed for taking part in STEPCARE, OHCA survivors eligible to take part in V-CARE are also required to have an mRS ≤ 3 at the 30-day follow-up and (a) must not have a diagnosis of dementia that would impact their ability to participate and benefit from the sessions and complete baseline/outcome measure (based on a clinician’s evaluation and/or self-report by the patient or family) and (b) must not be actively psychotic/experiencing any other serious acute mental health condition that would affect their participation in this study, based on clinical evaluation.

When recruited, consenting patients will be encouraged to take part in the study together with a ‘key supporter’; however, this will not be a requirement.

Consenting patients will be randomized on an equal basis (1:1) to the V-CARE arm or to the information booklet arm. V-CARE has a randomized block design with a separate randomization list in each country, completed by a local lead site. Custom-built software was developed using Python (v3.12.7) and the Tkinter library to allocate patients into two study conditions—V-CARE or the digital information booklet. A computer-generated pseudo-randomized list with 25 sets of 2 unique numbers per set was pre-generated using an online randomization tool [https://www.randomizer.org/] (accessed on 7 October 2024) to ensure an unbiased allocation process.

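### The arm comparison leaves out country, although randomisation is stratified by it, and the only multivariable model named is logistic, although most outcomes are scale scores

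*Protocol article*

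**What the plan says.** Section 2.3 (Study Population and Randomization) makes country a stratum: "V-CARE has a randomized block design with a separate randomization list in each country, completed by a local lead site". Allocation is 1:1, and the list is described as "A computer-generated pseudo-randomized list with 25 sets of 2 unique numbers per set", which reads as blocks of two.

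Section 2.6 (Data Collection, Statistical Analyses, and Sample Size) then makes three separate statements:

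- Arm comparison: "To assess differences between two groups, the analyses will be conducted using independent data, with tests appropriate to the distribution of the data". The tests named are the independent t-test and the Mann–Whitney U test, with effect sizes and 95% confidence intervals.
- Regression: "Multi-variable logistic regression models will be used to evaluate the associations between disease severity, sociodemographic variables, and outcome measures". Trial arm is not mentioned in this sentence.
- Adjustment: "Outcomes will be statistically controlled for potentially confounding variables such as age, sex, education, and length of intensive care stay". The sentence does not say which model does this, and country is not in the list.

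Sections 2.5.2 and 2.5.3 list the outcomes. CSQ-8 and SMASc are scale scores, as are most of the STEPCARE follow-up measures (MoCA, SDMT, HADS, PCL-5, WHODAS 2.0, ZBI and others). The only cut-off given is 24/32 on CSQ-8, and it is a progression criterion for the V-CARE arm.

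The target is at least 50 randomised patients. Section 2.6 calls the comparisons exploratory and underpowered. The Conclusions nevertheless intend to use between-group differences to help choose the primary outcome of the larger trial and to work out its power.

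**The concern.** There are two distinct problems.

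First, the analysis does not follow the randomisation. Separate lists keep the arms balanced within each country, so country differences contribute almost nothing to the true sampling error of the arm difference. A two-sample test does not know this. It counts country variation as noise and reports an interval that is too wide. The SD it yields also mixes within-country and between-country spread, which is a poor input for sizing the next trial.

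Second, the regression named does not match the outcomes listed. Ordinary logistic regression needs a binary outcome, so a scale score would have to be cut, and no rule for this model is given. With about 50 patients, a cut score and several covariates leave few events per parameter. Odds ratios then tend to be too large and can fail to converge. The adjustment sentence has no clear home either, because a t-test or Mann–Whitney test cannot adjust for covariates.

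**Working it through.** **Sample size.** Section 2.6 screens at least 145 and assumes 35% are randomised: 145 × 0.35 = 50.75, which agrees with the stated 50. With drop-out at the green limit of 20%, 50 × 0.80 = 40 are analysed. The range is therefore 40–50.

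**Part 1: leaving out country.**

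Assumptions (the document gives no country difference or split): the countries differ by d within-country SDs, half the patients come from each, and the arms are balanced within country.

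- Variance of a score with country ignored: 1 + 0.5 × 0.5 × d² = 1 + d²/4, in units of the within-country variance.
- Ratio of reported to correct standard error: √(1 + d²/4).
- d = 0: ratio 1.000, no effect.
- d = 0.5: √1.0625 = 1.031, about 3% too wide.
- d = 0.8: √1.16 = 1.077, about 8% too wide.
- An uneven split makes the effect smaller, because p(1 − p) is largest at p = 0.5.

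A simulation with 50 patients, 25 per country, and an assumed arm effect of 0.8 SD agrees:

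| Country difference | Power, t-test | Power, linear model with country | Type I error, t-test | Type I error, linear model |
|---|---|---|---|---|
| 0 SD | 80% | 80% | – | – |
| 0.5 SD | 78% | 80% | 4.6% | 4.9% |
| 1 SD | 70% | 79% | 3.1% | 5.0% |

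The error is on the conservative side.

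**Part 2: the logistic model.**

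Events per parameter = N × event rate ÷ number of parameters. The document gives neither an event rate nor a parameter count, so both are assumed: event rates of 20–50% and 4 to 7 parameters. Four corresponds to the named covariates; seven adds severity, arm and country, each counted once.

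- N = 50, lowest: 50 × 0.2 ÷ 7 = 10 ÷ 7 = 1.4.
- N = 50, highest: 50 × 0.5 ÷ 4 = 25 ÷ 4 = 6.2.
- N = 40, lowest: 40 × 0.2 ÷ 7 = 8 ÷ 7 = 1.1.
- N = 40, highest: 40 × 0.5 ÷ 4 = 20 ÷ 4 = 5.0.
- Middle case, N = 50, 30% events, 6 parameters: 15 ÷ 6 = 2.5.

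The overall range is 1.1 to 6.2. By contrast, a linear model with arm, country and two covariates has 50 ÷ 4 = 12.5 observations per parameter, or 40 ÷ 4 = 10.

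A second simulation shows what would happen if a six-parameter logistic model on a cut score did carry the adjusted arm comparison, which the plan does not state (N = 50, assumed 0.8 SD effect):

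| Event rate | Power, logistic | Power, linear | Mean log odds ratio (large-sample value) | Near-separation |
|---|---|---|---|---|
| 50% | 58% | 74% | 1.54 (1.31) | 0.1% |
| 30% | 51% | 75% | 1.68 (1.34) | 2% |
| 20% | 34% | 73% | 1.72 (1.42) | 11% |

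At 30% events the log odds ratio is 1.68 ÷ 1.34 = 1.25 times its large-sample value, that is, about 25% too large.

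**The case against.** The strongest reply is that little is at stake and that much could sit in a fuller plan. The primary outcomes are descriptive, with progression tests that neither problem touches. The arm comparisons are declared exploratory and underpowered, with no effectiveness conclusion to be drawn. The covariate list is open-ended, so country is unnamed rather than excluded. A condensed article may leave model details to an analysis plan. The loss from omitting country is only a few per cent unless the countries differ a great deal.

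Most of this stands, and it limits the weight of the point. It does not remove it. The article does not leave the arm comparison open: it names tests that cannot include the stratum, and it names a regression type that does not suit most of the outcomes. The between-group differences are also meant to inform the larger trial.

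Some stronger readings are not supported:

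- A reader might infer that the arms are compared by logistic regression. They are not. The logistic sentence concerns severity and sociodemographic associations, and it is only unclear whether the adjustment sentence belongs to it.
- A reader might infer that every scale score will be dichotomised. The text does not say so. Return to work, completion, and CSQ-8 below 24/32 could be the binary outcomes intended.
- A reader might take a narrow figure such as 2–4 events per parameter as given. Any such figure depends on assumed inputs.
- A reader might think that omitting country biases or overfits the arm estimate. It does neither. Sparseness concerns only the logistic model.
- Different usual care in the two countries is not documented. Different languages are, through the Swedish translation in section 2.2.

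**Conclusion.** The point holds in two limited parts.

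The arm comparison ignores the stratum used in randomisation. The estimate stays unbiased, but the interval is too wide: not at all if the countries do not differ, about 3% at 0.5 SD and 8% at 0.8 SD. These country differences and the equal split are assumptions.

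The only multivariable model named is logistic, while nearly all the named outcomes are scale scores. If it is used for them, they must be cut, and the model would have roughly 1 to 6 events per parameter in 40–50 patients, on assumed event rates of 20–50% and 4–7 parameters. The promised covariate control has no stated model, and the tests named for the arm comparison cannot supply it.

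Neither part affects the feasibility, tolerability or satisfaction criteria. The change is worth making because it costs almost nothing and the estimates feed the design of the larger trial.

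**What to change.** In section 2.6, make these changes:

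- Estimate the arm difference for each scale score with a linear model on arm and country, plus at most one or two covariates named in advance (for example age). Report the adjusted mean difference with its 95% CI.
- State that this model carries the covariate control.
- Restrict logistic regression to truly binary outcomes such as return to work, name those outcomes, and use a penalised (Firth) fit.

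This changes the analysis wording only. It needs no new data and no change to randomisation or sample size. The downside is that fewer covariate associations are explored, which is reasonable with about 50 patients.
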